## Abstract

**Introduction::**

The increasing prevalence of obesity worldwide necessitates the provision of support for many patients. Patients with obesity appreciate receiving advice from doctors. Previous studies have qualitatively explored clinicians’ counseling for weight loss; however, this is limited to primary physicians or general practitioners working in community health centers. In contrast, Korean Medicine Doctors (KMDs) have treated patients with obesity using a holistic approach with a multicomponent approach on counseling. However, there is currently no data regarding KMDs’ consulting practices for weight loss. Therefore, the present study will explore KMDs’ experience in counseling for weight loss and describe the constituents of counseling for weight loss in Korean medicine practice.

**Methods::**

This qualitative study utilizes a phenomenological framework. The KMDs who have worked >1 year as practitioners in treating patients with obesity will be invited to describe their lived experiences of counseling patients for weight loss. Purposive and snowball sampling will be undertaken to ensure that the sample provides information-rich cases that are representative of KMDs’ experiences of counseling for weight loss. Face-to-face, individual, and semi-structured interviews will be conducted with the participants, which will be analyzed using a phenomenological method.

**Ethics and dissemination::**

Ethical approval was granted by the Human Research Ethics Committee of the Korea Institute of Oriental Medicine (I-1908/006-001). The results will be disseminated via journal articles and conference presentations.

**Trial registration number::**

Korean Clinical Trial Registry, KCT0004985.

## Introduction

1

Obesity is a well-known risk factor for increased morbidity and mortality as well as impaired quality of life. Its prevalence has increased worldwide in the past 50 years and reached a pandemic level, as over one-third of the world's population is now classified as obese.^[1,2]^ In South Korea, the number of people with high obesity, or those which have a body mass index (BMI) of >30, is expected to increase from 3.5% in 2005 to 9.0% in 2030.^[3]^ As the BMI increases, medical costs rise progressively and are expected to grow in the next 15 years.^[4]^ Moreover, socioeconomic loss due to obesity amounted to 7.5 billion USD in 2015, which has doubled in the last 10 years in South Korea.^[3]^ Only about 15% of obese patients succeed in weight loss; however, one-third of them return to their original weight while most of them fail after 5 years.^[5]^ So far, obesity treatment strategies have not been successful in the long term.^[2]^ Hence, obesity has been recognized as a chronic disease that needs to be managed continuously over an individual's lifetime.

Obesity is more than a simple energy imbalance. Subsequently, comprehensive and multicomponent approaches that include lifestyle or behavioral training, dietary changes to reduce energy intake, and increase in physical activity have started to attract attention. Good practice can involve counseling that includes comprehensive education, lifestyle advice, and psychological support.^[4]^ For example, even the dietitian's role has transformed from being a nutrition educator to being a counsellor over the last 20 years. There has also been a concurrent shift in weight loss philosophies and practice guidelines.^[6]^ Several guidelines have been developed to assist healthcare professionals in the treatment of obesity and promote effective counseling.^[7,8]^ Doctors use these guidelines as basis for outlining counseling strategies for obesity which include lifestyle changes, dietary modification, and increased physical activity.^[4]^ In a way, counseling is the key means to stabilize the patients’ psychological urge to overeat, correct their knowledge on weight loss, and eventually balance their input and output of energy.

Previous studies have demonstrated the effectiveness of counseling for weight loss (i.e., counseling itself, or counseling combined with medicine).^[9–12]^ Using qualitative study, they have explored the clinicians’ approach to weight counseling, including what advice to provide during a routine consultation.^[13–18]^ So far, the interviewees of the previous studies have been limited to primary physicians or general practitioners working in community health centers. Accordingly, they focused on how doctors raise the topic of obesity with patients who come to their clinics for other reasons. In those situations, counseling for weight loss is easily overlooked and doctors tended to have negative attitudes towards it.^[14–16,18]^

Korean Medicine (KM), a conventional health care covered by the national medical healthcare system, are playing an important role in the National Health Service of South Korea especially for obese patients.^[19–21]^ Since previous studies in KM have confirmed its effectiveness, KM therapies such as acupuncture, herbal medicine, and counseling are frequently used to treat obesity.^[22–24]^ Especially, counseling is considered as an essential practice that improves the patient's understanding and participation, and leads to the patient's behavioral modification. A manual for standard counseling for obese patients in KM was developed by recognizing counseling as an important factor in the treatment of obesity.^[8]^ The manual covers pattern identification, and Sasang constitution to classify patients into 6 patterns and 4 constitution respectively to prescribe herbs or manage prognosis factors like abdominal obesity. However, there is currently no data on the consulting practices of Korean Medicine Doctors (KMDs) related to weight loss.

Phenomenology is a philosophical approach used in describing the internal meaning and structure of experience.^[25]^ Thus, this approach is useful in understanding the essential meaning of counseling in KM practice for treating patients with obesity, and researching the essential structure of human experience.^[26]^ In applying this, researchers will use the qualitative method to describe the KMDs’ counseling for weight loss and the constituents of counseling for weight loss in KM practice.

The study aims to explore the experiences of KMDs when they advise about weight loss. Specifically, this study aims to investigate the following research questions: What are the experiences of KMDs while they provide counseling for weight loss? How do KMDs decide what to say to their patients for their weight? What are the KMDs’ perceptions and attitudes towards counseling in the management of obesity? What are the objectives and roles of counseling in the management of obesity? What advice do KMDs provide during counseling for weight loss? What do KMDs say to their patients about their weight? What is the difference between the KMD's counseling and obesity counseling by other experts, such as dietitians or personal trainers? As individual treatment is emphasized in the management of obesity, what are the individual strategies in counseling?

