### Qualitative study design

2.1

This research will employ a qualitative design to explore the experiences of KMDs in counseling for weight loss. We chose the qualitative descriptive approach because it provides broad and rich information and straightforward descriptions of the participants’ perspectives on counseling for weight loss. Moreover, we chose this approach for its usefulness in gaining a preliminary insight into a topic and collecting the first-hand experiences of participants. Lastly, the conduct and reporting of this study will be in accordance with the Consolidated Criteria for Reporting Qualitative Research checklist for interviews to ensure rigor, comprehensiveness, and credibility.^[27]^

This study will be situated within a phenomenological framework as we are attempting to understand the experiences of KMDs on counseling for weight loss.^[28,29]^ Moreover, we used the phenomenological framework since it requires the researchers to examine the issue by collecting data from individuals who have first-hand experience. According to Husserl and Moran,^[30]^ the best way to study a phenomenon is to go back to “the things themselves.” Therefore, we will go back to the KMDs to gain a valid understanding of their personal experiences and perceptions of counseling in the treatment of obesity.

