### Study sample and recruitment

2.2

Researchers will interview up to 15 KMDs who have experienced counseling for weight loss, and recruit them using purposive or snowball sampling. Purposive sampling is the method in which a researcher intentionally approaches participants who are suitable for research and selects them.^[31]^ Since creating specialized obesity clinics that focus on obesity management has become a trend, the number of hospitals operating obesity clinics has increased rapidly,^[32]^ with >3000 obesity clinics in Seoul alone.^[33]^ Because of this, the Society of Korean Medicine for Obesity Research (SKMOR), with a membership of >500 KMDs who have worked in specialized obesity clinics, was established. Hence, researchers will contact the SKMOR to look for qualified people who are interested to be participants in our study. One of the researchers (KH) is an editorial director of the SKMOR, and she will have participant contact. On the other hand, snowball sampling is the method in which participants introduce applicants to the researcher,^[34]^ where suitable applicants are registered as participants.

The recruitment of the research participants, the interviews, and the analysis of the interviews will be performed at the same time. When we have repeated the interviews and analyses, there will be a time when no new themes are being generated, which is called “data saturation.”^[35]^ When data saturation is reached, researchers will stop recruiting participants.

The potential participants will be provided with information about the aims and methods of the study and be assured that their confidentiality and privacy will be maintained. The potential volunteer recruits will also be informed that they are free to withdraw from the study at any time. Those agreeable to participating will provide written and informed consent.

The inclusion criteria will include doctors who finished their 4- or 6-year course in a nationally accredited KM university, have a KMD license certified by the Ministry of Health and Welfare in South Korea, and have experience as practitioners of medical management for weight loss for >1 year. The exclusion criteria will be those who did not agree to participate and considered to be inappropriate by the researchers (i.e., counseling time is <5 minutes).

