### Data collection and recording

2.3

This study will be conducted from September 2019 to October 2020. Two researchers with experience in managing patients with obesity and qualitative research will conduct the interviews. The main method of data collection will be in-depth interviews that use open questions and semi-structured follow-up interviews (Table 1). Examples of questions for the KMDs include “What do you say to patients about their weight?” “What is the priority in the management of obesity?” “What do you advise about weight loss?” “What are the objectives and the role of counseling in the management of obesity?” “How important is counseling for the outcomes and prognosis of obesity?” “What is the difference between KMD's counseling and obesity counseling by other experts, such as dietitians or personal trainers?” “During the management of obesity, individual treatment is emphasized; what are the individual strategies in counseling?” and “Is standardized counseling available according to the guidelines about consultation for obesity?”

**Table 1 T1:** Interview guide.

Topic	Main question	Probe
Introduction	Interviewers will state the purpose and notice of this interview to interviewees and create a comfortable atmosphere prior to the full-scale theme and aim to identify the interviewee's profileGreetings, words of appreciation, and reminders (e.g., to turn off the mobile phones)Introduction of researchersExplanation of the purpose of the interviewExplanation of how to proceed	
Warm-up questions (demographic characteristics)	Overview of KM treatment for obesity“Please tell us about the counselling for patients with obesity currently being done in KM clinics.”Status of obesity care, number of patients, consultation period, etc.“How important is counselling in treatment outcomes and prognosis of weight loss?”	
Main questions	Core contents of KM counseling for weight loss“What is the purpose of counselling?”“What should be the first approach in counselling?”“Compared to other obesity specialists such as dietitians and exercise therapists, what makes KM counselling different?”“How important is pattern identification in counselling for weight loss?”“How important is Sasang constitution is in counselling for weight loss?”	Personal experience

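### One research question is worded as a factual difference between KMD counseling and that of other experts, but the data can show only how KMDs perceive that difference, and the matching interview items lead

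*Protocol article*

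**What the plan says.** The last paragraph of the Introduction opens with the overall aim, "The study aims to explore the experiences of KMDs when they advise about weight loss", and then lists eight research questions. The seventh is "What is the difference between the KMD's counseling and obesity counseling by other experts, such as dietitians or personal trainers".

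The section on study sample and recruitment fixes who supplies the data: "Researchers will interview up to 15 KMDs who have experienced counseling for weight loss". Eligibility requires, among other things, that participants "have a KMD license certified by the Ministry of Health and Welfare in South Korea" and have more than one year of practice in weight management. Recruitment runs through the Korean medicine obesity society or by snowball sampling. Contact with dietitians, trainers or exercise therapists is not a criterion.

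The section on data collection and recording describes the source of data: "The main method of data collection will be in-depth interviews that use open questions and semi-structured follow-up interviews". Field notes and observed bodily expressions supplement the recordings. The sample questions in that section's text repeat the research question almost word for word. The corresponding main question in Table 1 reads: "Compared to other obesity specialists such as dietitians and exercise therapists, what makes KM counselling different".

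**The concern.** Read literally, the research question asks what separates two kinds of counseling. The study has direct data on one kind only. What a KMD says about a dietitian's counseling may come from joint work, from referrals, from patients' remarks or from general impression, and the guide has no item that would tell these apart.

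The items also assume the answer to a prior question. They ask what the difference is, or what makes Korean medicine counseling different, without first asking whether anything differs. Participants describe their own profession, and many will come through its own obesity society or by peer referral. In that setting a presuming item pushes towards naming a distinction.

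The stake is how the result will be read. The Discussion expects the findings to feed revision of the counseling manual and possibly policy on insurance coverage. A statement that KMD counseling differs from that of other experts would carry more weight there than these data can bear, unless it is labeled as the KMDs' own view.

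**Working it through.** The article gives no figure on this point, so the check sets its sections side by side.

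1. **Wording of the question.** The Introduction lists eight research questions, in order: experiences while counseling; how KMDs decide what to say; perceptions and attitudes; objectives and roles; advice given; what is said about weight; difference from other experts; individual strategies. Only the seventh sets KMDs against another group. The third is limited to perceptions by its own words; the seventh is not. The fourth and eighth also lack such a limit, so its absence from the seventh does not show that a factual comparison was meant.

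2. **Who can answer.** Participants number up to 15, and all must hold a KMD license. Recruitment provides for no sample of dietitians, trainers or exercise therapists, and none of patients. One side of the comparison has direct informants; the other has none.

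3. **What informants must know.** The design section gives as a reason for the phenomenological framework that "it requires the researchers to examine the issue by collecting data from individuals who have first-hand experience". Every participant has that experience of KMD counseling. Nothing in the criteria ensures it for counseling by the other professions. For that half of the comparison, the data are the KMD's view from outside.

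4. **What scope the plan sets.** The design section says "we will go back to the KMDs to gain a valid understanding of their personal experiences and perceptions of counseling". The overall aim and the Discussion speak likewise of KMDs' experiences and perspectives. So the plan's own scope is perception, and the seventh question is worded more widely than that scope and than the data.

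5. **How the items elicit the answer.** Neither the sample question in the text nor the Table 1 item asks whether there is a difference, or what is the same. Table 1 lists personal experience as a probe against the main questions. That steers the KMD towards experience, but it is generic and does not ask about exposure to the other professions.

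6. **Which comparators.** The research question and the sample question name dietitians and personal trainers. Table 1 names dietitians and exercise therapists. Only dietitians appear in all three places.

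Steps 1 to 4 show a mismatch of wording between one question and its data. Step 5 shows a leading item. Step 6 shows an inconsistency in the comparator.

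**The case against.** The strongest reply is that the question is already limited to KMDs' views. It appears as a sub-question of an aim about their experiences; the design section and the Discussion repeat that scope; and other questions in the list are worded just as briefly. A phenomenological study of one profession needs no comparator group. Its call for first-hand experience concerns the phenomenon studied, which is KMDs' own counseling, and every participant has that. Most of this stands. It means that the sample and method suit the stated aim, and that a fair reader may take the question as one about perceived difference. It does not make the question say so, and it does not cure the leading items.

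Several stronger readings are tempting, but the article does not support them:

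- **That the items cannot return an answer of no difference.** The interviews use open questions with semi-structured follow-up, and a participant can reject the premise. The items discourage that answer; they do not exclude it.
- **That guesses will count equally with informed accounts in the analysis.** The data analysis section does not say how the two are handled, and in a condensed article that silence is not evidence of equal treatment.
- **That the study plans to claim a difference between professions.** The Discussion lists no cross-profession comparison among its expected outputs. The risk lies in how an answer to the question as worded might be reported or cited.

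**Conclusion.** The point holds as an inexpensive improvement to stated text. One of eight research questions is worded more widely than its data, which come from up to 15 KMDs and from no member of the comparison professions. Those data can support only the KMDs' perceived difference, and that is what the overall aim asks for. The interview items on this question presume a difference, and the comparator professions are not named consistently.

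A reader might infer that the design has failed, or that dietitians and trainers must be added. That would follow only if a factual comparison were intended, and the stated aim points the other way. The other seven questions are unaffected.

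The conclusion assumes that the criteria, sample questions and Table 1 are as printed. How far the leading wording would shift the answers cannot be quantified from the article.

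**What to change.** - **Research question.** Reword it as: *How do KMDs perceive their counseling to be similar to or different from that of other experts?*
- **Exposure first.** In the guide, ask: *Have you worked with, referred to or seen counseling by these professionals?*
- **Neutral item.** Then ask: *What, if anything, is the same and what is different?* Change both the sample question in the text and the Table 1 item.
- **Same comparators.** Name the same professions in the research question, the sample question and Table 1.
- **Reporting.** Present the result as KMDs' perception and note whether each account rests on direct exposure.

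The cost is the rewording, about one minute per interview, and a more modest claim. Sample, recruitment and method of analysis stay as they are.

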## Methods and analysis

2

### Qualitative study design

2.1

This research will employ a qualitative design to explore the experiences of KMDs in counseling for weight loss. We chose the qualitative descriptive approach because it provides broad and rich information and straightforward descriptions of the participants’ perspectives on counseling for weight loss. Moreover, we chose this approach for its usefulness in gaining a preliminary insight into a topic and collecting the first-hand experiences of participants. Lastly, the conduct and reporting of this study will be in accordance with the Consolidated Criteria for Reporting Qualitative Research checklist for interviews to ensure rigor, comprehensiveness, and credibility.^[27]^

This study will be situated within a phenomenological framework as we are attempting to understand the experiences of KMDs on counseling for weight loss.^[28,29]^ Moreover, we used the phenomenological framework since it requires the researchers to examine the issue by collecting data from individuals who have first-hand experience. According to Husserl and Moran,^[30]^ the best way to study a phenomenon is to go back to “the things themselves.” Therefore, we will go back to the KMDs to gain a valid understanding of their personal experiences and perceptions of counseling in the treatment of obesity.

### Study sample and recruitment

2.2

Researchers will interview up to 15 KMDs who have experienced counseling for weight loss, and recruit them using purposive or snowball sampling. Purposive sampling is the method in which a researcher intentionally approaches participants who are suitable for research and selects them.^[31]^ Since creating specialized obesity clinics that focus on obesity management has become a trend, the number of hospitals operating obesity clinics has increased rapidly,^[32]^ with >3000 obesity clinics in Seoul alone.^[33]^ Because of this, the Society of Korean Medicine for Obesity Research (SKMOR), with a membership of >500 KMDs who have worked in specialized obesity clinics, was established. Hence, researchers will contact the SKMOR to look for qualified people who are interested to be participants in our study. One of the researchers (KH) is an editorial director of the SKMOR, and she will have participant contact. On the other hand, snowball sampling is the method in which participants introduce applicants to the researcher,^[34]^ where suitable applicants are registered as participants.

The recruitment of the research participants, the interviews, and the analysis of the interviews will be performed at the same time. When we have repeated the interviews and analyses, there will be a time when no new themes are being generated, which is called “data saturation.”^[35]^ When data saturation is reached, researchers will stop recruiting participants.

The potential participants will be provided with information about the aims and methods of the study and be assured that their confidentiality and privacy will be maintained. The potential volunteer recruits will also be informed that they are free to withdraw from the study at any time. Those agreeable to participating will provide written and informed consent.

The inclusion criteria will include doctors who finished their 4- or 6-year course in a nationally accredited KM university, have a KMD license certified by the Ministry of Health and Welfare in South Korea, and have experience as practitioners of medical management for weight loss for >1 year. The exclusion criteria will be those who did not agree to participate and considered to be inappropriate by the researchers (i.e., counseling time is <5 minutes).

